## Study objective

2

The objective of this study is to investigate the impact of a pragmatic lifestyle intervention during, and post pregnancy compared with routine care, on weight reduction at 12 months postnatal in overweight women with previous GDM (PAIGE2). The primary outcome will be the percentage maternal weight loss over a 12-month period. Secondary outcomes will include maternal glucose tolerance, anthropometry, number of steps per day, and several questionnaires detailing physical activity and health and wellbeing, to assess clinical, anthropometric and lifestyle- related health and well-being measures. This protocol follows the reporting guidelines of the Standard Protocol Items: Recommendations for Interventional Trials (SPIRIT) Checklist and World Health Organization Trial Registration Data Set (**Supplementary Materials 1**, **2**).

## Methods and analysis

3

### Design

3.1

#### Pilot study

3.1.1

The study has been designed and developed based on results of a recently completed pilot RCT (PAIGE) (52). The study, which was informed by focus groups, clearly highlighted the demands on these women and the key issues to consider in future lifestyle interventions, including the need for simplicity, to involve partners/and or families, to consider supportive care and be open to partnership between CWMOs and NHS. The PAIGE2 study, whilst having similar overall objectives to PAIGE, has been specifically modified to reflect the information gained from PAIGE participants and in particular the challenges of the women in the postnatal period. As part of the initial PAIGE pilot, study focus groups were carried out with participants who completed the study. As a direct consequence of this feedback, PAIGE2 has been designed to make it easy for women to take part and to remain in the study, with recruitment now taking place during pregnancy at routine review clinics rather than at 6–8-week follow-up visit, which was challenging for women to attend and had high attrition rates.

The PAIGE2 research proposal has been reviewed by women with GDM during a recent pregnancy prior to submission thus ensuring that researchers complete the circle of patient involvement in the proposal. In addition, service users and the public will be closely involved in the study and women with a history of GDM will be invited to sit on the Project Board. The involvement of users within the research process will be an important guide to local researchers in finalizing wording for patient information sheets, local recruitment strategies and in relation to supporting women while on the intervention.

#### Study setting

3.1.2

A six center, two parallel arm, randomized controlled trial, with an equal allocation ratio of intervention to control group participants will be conducted. The six centers will include antenatal-metabolic clinics at the Royal Jubilee Maternity Service, Belfast; Ulster Hospital, Dundonald; Antrim Area Hospital; Our Lady of Lourdes Hospital, Drogheda; Sligo University Hospital and Letterkenny University Hospital.

#### Recruitment

3.1.3

All pregnant women with a BMI ≥25 kg/m^2^, recently diagnosed with GDM using IADPSG criteria (45) (either by an oral glucose tolerance test (OGTT) or a high random blood glucose result) around/between 28-30 weeks gestation, will be invited to join the study. Following a positive GDM diagnosis, woman will be referred to the joint metabolic antenatal clinic. A member of the woman’s usual multidisciplinary diabetes care team will seek the woman’s permission for her to be contacted by the PAIGE2 research team *via* a contact number provided by the woman. Women will be provided with an information sheet informing them of the study by a member of the usual diabetes care team. Women will be advised to take it home, read it thoroughly and speak to family and friends before deciding whether to participate.

Before their routine 32–36-week gestation antenatal diabetes clinic appointment, women will be contacted by a member of the PAIGE2 research team *via* the contact number provided to the diabetes care team, to answer any additional questions and confirm their interest in taking part. The participants will be informed that the study is designed to explore the feasibility of a pragmatic lifestyle intervention customized to the postnatal period, and if participants meet the study inclusion criteria (listed below), they will be randomized either to the lifestyle intervention or to usual care.

Informed consent will take place approximately 2-6 weeks after the patient is first given a patient information sheet, by a member of the PAIGE2 research team. The PAIGE2 researcher will ensure that the participants have read and understood the participant information sheet, offer further explanation, if necessary, confirm eligibility and obtain written consent prior to their enrolment in the PAIGE2 study. Only after consent has been provided by the women, will any member of the PAIGE2 research team have access to the woman’s health information. If the women have a partner, they will be given the opportunity to be involved in the study, subject to written consent.

#### Randomization

3.1.4

To streamline the organization of the intervention, economize on staff time and avoid contamination effects, women will be randomized to treatment group according to the week they attend for review at the joint diabetes antenatal clinic at 32-26 week’s gestation. Delivery of the intervention or control program will take place weekly at each site in person or *via* telephone or video call. Weeks will be allocated at random, using a restricted randomization developed earlier. To minimize the risk of manipulation, allocations will only be made available to recruitment centers on the morning of the visit in sufficient time for necessary administrative arrangements to be made. Women who agree to participate at 32–36-week gestation but who did not subsequently turn up for their postnatal follow-ups must be considered as having been recruited but lost to follow-up. Due to the nature of the intervention, the study cannot be blinded. The number of women randomized to each schedule will be reviewed regularly by the trial statistician to ensure that approximately equal numbers are assigned to treatment group. Should a serious imbalance develop, an additional intervention or control week will be added as appropriate.

#### Inclusion criteria

3.1.5

Inclusion and exclusion criteria for this study are similar to that of the original PAIGE study (52).

Women aged ≥18 years.Booking BMI ≥25 kg/m^2^ at <14 weeks gestation.GDM diagnosed in the current pregnancy. GDM will be defined by the WHO (2013) criteria (46) (fasting plasma glucose (FPG) ≥ 5.1 mmol/l or 1h postprandial glucose ≥ 10.0 mmol/l or 2h plasma glucose ≥8.5 mmol/l). Women with a history of GDM directly prior to the current pregnancy, and who were given lifestyle advice and were performing self-monitoring of blood glucose from early pregnancy, will also be included if capillary glucose monitoring exceeds target values (fasting ≥ 5.3 mmol/l (95 mg/dl) or 1h postprandial plasma glucose ≥ 7.8 mmol/l (140 mg/dl)) thus negating the need for an OGTT (52).Women will only continue to be included in the study if their fasting plasma glucose the morning after delivery or at 6 weeks postpartum is either normal or consistent with impaired fasting plasma glucose outside of pregnancy (i.e., <7 mmol/l). (If the woman requests an earlier discharge that does not allow time for the immediate post-delivery FPG test, she will be offered an appointment to return to the maternity unit within 4-6 weeks of birth for retesting) (52).

#### Exclusion criteria

3.1.6

Pregnancy in which an anomaly has been detected on the 20-week fetal anomaly scan.History of diabetes outside of pregnancy or FPG ≥7 mmol/l the morning after delivery or at 6 weeks postpartum (these women will be excluded and referred to the local diabetes care team)History of heart, liver, or chronic renal disease.Medications that adversely affect glucose tolerance (e.g., steroids).Inability to participate in moderate physical activity outside of pregnancy.Moderate/severe depressive illness or excess alcohol consumption.Inability to understand adequately verbal explanations or written information in English, or special communication needs.Women who are planning another pregnancy within the next 12 months following delivery.Women who are intending to attend a CWMO program after pregnancy.Exclusion criteria for early postpartum glucose testing will include massive postpartum hemorrhage, steroid treatment prior to delivery or patient refusal.

#### Sample size

3.1.7

Assuming the same variability in weight loss as was observed in the pilot study (52) (standard deviations of 7.0 and 3.9 kg in the intervention and control groups, respectively) and a 40% drop out rate (including women diagnosed with overt diabetes on the basis of a fasting glucose sample postnatal), it is estimated that a trial of 340 women should yield 200 evaluable subjects (100 in each of the intervention and control groups) which will be sufficient to detect a 3kg difference in maternal weight at 12 months after delivery with >90% power at the 5% level of significance.

### Interventional methods

3.2

#### Intervention group

3.2.1

The education program will be delivered in person or by telephone or video call. The program will comprise one session lasting 60 minutes, delivered either in the hospital setting or by telephone or video call by a research nurse or dietitian both trained in motivational interviewing. The content will be underpinned by the principles used in the DPP (53) and will be designed to augment the further information received from the CWMO. The educational program will take account of socioeconomic status and ethnicity and will be specifically customized to post-pregnancy as informed by previous focus groups and guided by the existing literature, contextual factors impacting on nutrition and physical activity.

The intervention program will broadly be divided into the same information as the original PAIGE study (52): one third of the time talking about the “causes, consequences, difficulties, timelines and implications of GDM and overweight/obesity” (52), one third discussing advice regarding a healthy nutritional approach (52), and the remaining third tackling the supposed success of physical activity as an alternative treatment for the prevention of T2D and potential future GDM, including recommendations, barriers and strategies (52). The program will be modelled on the person-centered philosophy and techniques created to stimulate lifestyle modification and self-management in keeping with the Medical Research Council’s framework for complex interventions (54), updated in 2021 (55).

At 6-8 weeks, all postpartum mothers in the intervention group will be offered a free 12-week voucher for a CWMO (Slimming World). This voucher can be used by the participant to attend a local or online group of their choosing, run by Slimming World, for 12 consecutive weeks. Slimming World is group-based, and the mothers can enroll at any time. Meetings convene in community locations or online and are usually 90 minutes in duration. Mothers can also avail of a website, magazines and one to one telephone support from a Slimming World consultant or other Slimming World members. Like the original PAIGE study (52), the women in the study will be urged to consume foods predominantly with low energy density to reach satiety, including foods high in nutrients such as calcium and fiber, with restricted quantities of high energy dense foods. Principal behavior strategies used in Slimming World include weekly weighing, group support and commendation for weight loss, and sustained dedication regardless of amount of weight lost. Individualized support, if required, involves self-monitoring of diet and emotional eating, for and against assessments, visualization techniques and individual diet plans. Individual weight loss goals will be set by each mother. Physical activity is also promoted, with gradual increase to 30 minutes of moderate-to-intense activity 5 days per week. Slimming World’s theoretical underpinning is modelled on motivational interviewing and transactional analysis.

#### Control group

3.2.2

Women in the control arm will receive routine antenatal care as offered by their individual maternity hospital. When the study is concluded, the control group will be offered referral to Slimming World (12 consecutive weeks) free of charge and will be given access to the educational resources from the one-hour educational session.

#### Study timepoints

3.2.3

The study will involve four data collection appointments with the participants, as depicted in **Figure 1**.

**Figure 1 f1:**
[figure not shown]
Study Flowchart.

##### Timepoint one

3.2.3.1

Timepoint one will be the first study contact and will take place over the phone before 32-36 weeks gestation. Informed consent will be obtained at this point, followed by collection of baseline clinical and demographic data and questionnaire completion. Relevant clinical and obstetric data will be abstracted from patient notes and recorded in study specific case report forms.

Those women randomized to the lifestyle intervention will be enrolled into the study in small groups where they will receive an educational program lasting around one hour (as described above). They will also be given an activity tracking device (Fitbit) to allow them to become familiar with this technology during pregnancy. This device will either be posted to participating women or collected from research staff at the women’s next antenatal appointment. The education program will be led by a PAIGE2 research nurse or dietitian trained in motivational interviewing and will cover topics including GDM as a risk factor for future disease, healthy eating, physical activity, fitness tracker use, methods to reduce the risk of diabetes in subsequent pregnancies in the longer term, and ideas for maximizing peer support. The program will be loosely based on that used in the DPP (53) and designed to augment rather than duplicate the information the women will receive from Slimming World.

##### Timepoint two

3.2.3.2

Timepoint two is the second study contact and will take place at around 6-8 weeks postnatal when women attend routinely for OGTT. Women will be contacted at this visit to confirm their continuing willingness and eligibility to take part in PAIGE2. They will be weighed (or if this visit is not possible, they will be contacted and asked to weigh themselves and measure their waist circumference at home and forward their self-measured weight to the research staff). Alternatively, if they do not provide an OGTT, a fasting plasma glucose sample will be taken. All mothers (whether they provided an OGTT or fasting plasma glucose sample) will also provide a fasting blood sample to measure lipids and renal function. An additional serum sample will be stored for future analysis. This weight will function as a baseline measurement. The women will also be invited to upload their capillary glucose monitoring (glucometer) data during pregnancy to a secure website for examination in relation to other pregnancy-related variables such as physical activity. Those in the intervention will be offered a 12-week Slimming World voucher (free to the individual) to be completed within the 12-month period. This voucher can be used by the person to attend a group of their choosing, for 12 consecutive weeks. Women in the treatment group will be contacted by text messages (weekly for first month and then fortnightly) to provide motivation based feedback and to assess progress towards behavioral goals including a review of the step count, sleep activity and food intake.

Subsequent contact with the women will be by text or telephone a call. The frequency of contact by text message will be weekly for the initial month (to persuade the women to sign up for the CWMO) and then fortnightly for the remainder on the study. Structured telephone calls will occur monthly, and include information of physical activity, barriers to achieving their diet and physical activity goals, as well as suggested solutions. Participants who are successful during the first three-month period of enrolment with Slimming World (gauged by attending at least 9 out of 12 sessions or demonstrated weight loss), will be offered a second funded three-month membership to maximize any benefits obtained during the program. After the second free three-month Slimming World program, women will be able to continue to attend Slimming World for the rest of the study if they desire, at their own discretion. Partners of the women in the intervention arm will also be invited to participate in the trial. Partners consent will be obtained either by post or in person at the same 6-8 post gestational timepoint, and they will subsequently be offered a fitness tracking device like that of their partner. Intermittent contact *via* text will be made with the partner to feedback on their physical activity.

##### Timepoints three and four

3.2.3.3

At timepoints 3 and 4, the third and final study contacts, all women will be weighed (or asked to weigh themselves at home and forward their self-recorded weight to the research staff). They will also have an additional (fasting) blood sample taken, along with a measurement of their waist circumference and their blood pressure. In addition, they will be asked to complete the same questionnaires they answered at 32-36 weeks gestation.

#### Measurable outcomes

3.2.4

A summary of the several measurable outcomes of this study can be found in **Table 1**.

**Table 1 T1:** Measurable outcomes and their collection timepoints (TP).

Measurable outcome	Contact point measurement			
	*TP1*	*TP2*	*TP3*	*TP4*
Clinical history	x			
Anthropometric measurements (body weight, waist circumference, BMI)	x	x	x	x
Biochemistry measurements*		x	x	x
Step count (using Fitbit wearable fitness tracker) **	x	x	x	x
*Questionnaires*				
International Physical Activity (IPAC) 7day questionnaire	x	x	x	x
Risk Perception Survey for Developing Diabetes (RPS-DD)	x	x	x	x
Health and Wellbeing SF-12 Version 2	x	x	x	x
Edinburgh Postnatal Depression Scale		x	x	x
Motivation to Change Questionnaire	x	x	x	x
Exercise Self-Efficacy Questionnaire	x	x	x	x

TP1, Timepoint1 (32-36 weeks gestation); TP2, Timepoint 2 (6 weeks postpartum); TP3, Timepoint 3 (6 months postpartum); TP4, Timepoint 4, (12 months postpartum).

*Additionally taken initially day 1 postnatal, including fasting glucose, total cholesterol, triglycerides, high density lipoproteins, low density lipoproteins, non-high-density lipoproteins, cholesterol/high density lipoprotein ratio, urea and electrolytes.

** Used daily throughout the 12 months, also includes partners step counts (if applicable).

##### Primary endpoints

3.2.4.1

Weight at 12 months (accounting for any difference in weight at baseline between the intervention and control groups)

Body weight: Women will be weighed (to the nearest 0.1kg) when they attend their 6-8 weeks postnatal appointment performed as part of routine standard care and will act as the baseline measurement. If they are unable to attend the department for this, the women will be asked to weigh themselves at home 6-8 weeks postnatal and send their self-measured weight in a text message to the research staff.Height (to the nearest 0.1cm), to calculate BMI (kg/m^2^).

##### Secondary outcomes

3.2.4.2

1) Fasting glucose

Day 1 postnatal (Inpatient in hospital following delivery): A fasting venous blood sample will be taken for glucose measurement and a serum sample will be stored for future analysis.Timepoint 2 (6-8 weeks postnatal): Participants will confirm eligibility by an OGTT when they attend their postnatal routine standard care appointment, or alternatively a fasting plasma glucose sample will be taken, along with a fasting blood sample to measure lipids and renal function. An additional serum sample will be stored for future analysis.Timepoint 3 (6 months postnatal) and timepoint 4 (12 months postnatal): A maternal blood sample will be taken for fasting plasma glucose, lipids, and renal function. An additional serum sample will be stored for future analysis.

2) Waist circumferenceWaist circumference (midpoint between lower costal margin and iliac crest) (cm), hip circumference (cm).3) Step counts, change from baseline to 12 months (intervention group only).The Fitbit tracker will allow women and their partners to upload their daily data to a secure dedicated spreadsheet. Women will choose what form of activity to engage in such as walking, dancing, aerobic activity etc., and will be encouraged to set individualized step count goals based on their baseline step count. Accumulation of all activity across the day will be promoted. Sedentary participants will be encouraged to increase their activity levels by a minimum of 3,000 steps per day, equivalent to approximately half an hour of walking (56). Goal attainment will be encouraged using numerical objectives, for example, increasing steps by 500 steps per day every fortnight and encouraged to repeat this method for each new goal (52). They will also be encouraged to wear their fitness tracker daily to view and track their activity and will be prompted to record this by uploading the data onto a secure website.4) Questionnaires

Physical activity will also be recorded at all timepoints using two questionnaires. The International Physical Activity Questionnaire (IPAQ) (57) will provide a record of both light and moderate-to-vigorous intensity activities carried out for 10 uninterrupted minutes. The IPAQ has provided sufficient validity in comparison with accelerometer data in the UK. An exercise self-efficacy questionnaire will provide a measure of participants’ belief in their ability to exercise and will identify barriers including motivation and willingness to exercise in certain situations (58).The Risk Perception Survey for Developing Diabetes (RPSDD) (59), adapted for women with a history of GDM, is a self-reported or telephone interview questionnaire used to evaluate risk perception and modifiers of risk perception among women with a history of GDM who have not developed T2D postpartum (59). The instrument comprises 4 scales assessing “modifiers of risk perception, including patients’ knowledge of diabetes risk factors, perceptions of personal control, optimism about developing diabetes and other diseases, and perceptions of the benefits and barriers of preventive behaviors” (59). The survey takes approximately 5 minutes, also includes two scales evaluating actual risk perception.Psychological measures and health and wellbeing will be measured at all timepoints using the 12-Item Short-Form (SF-12v2) Health Survey (60).Postpartum depression will be assessed using the Edinburgh Postnatal Depression Scale at timepoints 2-4 (61).Motivation for change will be measured at all timepoints by asking two questions devised by the team. For women in the intervention group motivation for change will be measured both before the delivery of the one-hour educational session and after, to assess the influence of the session on motivation to change.

All the questionnaires have established reliability and validity.

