#### Statistical analysis

3.3.1

Primary and secondary outcomes at 12 months will be compared between the intervention and control groups using analysis of covariance to adjust for any differences at baseline and so produce an estimate of the intervention effect with 95% confidence limits. Adjustment will also be made for recruitment center and any characteristics relevant to the outcome which, by chance, show imbalance between groups. Prior to analysis, logarithmic transformations will be applied to those secondary outcome variables whose distributions show marked positive skew. A correction will be applied to standard errors of intervention effect estimates to make allowance for the clustered nature (by week) of the randomization, although analysis of the pilot study (which used the same randomization procedure) indicated that this will make little difference to the findings. To help assess the impact of non-response, sensitivity analyses will be conducted on key outcomes by multiple imputation of missing values by chained estimating equations using the commands provided in the Stata package (StataCorp, College Station, TX). We will use this approach to impute 10 complete datasets and analyze them appropriately to provide results which take account of missingness. For key outcome variables, this analysis will be reported in addition to the complete case analysis. Analysis will be by intention to treat.

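### The before-after change in motivation, measured in the intervention arm alone, cannot show the influence of the education session and should be reported as descriptive only

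*Protocol article*

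**What the plan says.** Section 3.2.4.2 (Secondary outcomes) says of the whole trial population: "Motivation for change will be measured at all timepoints by asking two questions devised by the team". It then adds an extra measurement in one arm: "For women in the intervention group motivation for change will be measured both before the delivery of the one-hour educational session and after", and gives the reason: "to assess the influence of the session on motivation to change". The section closes its account of the instruments with "All the questionnaires have established reliability and validity".

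Table 1 (section 3.2.4) lists the item among the questionnaires as "Motivation to Change Questionnaire" and marks it at all four timepoints, with no restriction by arm. At timepoint one (3.2.3.1), "Informed consent will be obtained at this point, followed by collection of baseline clinical and demographic data and questionnaire completion"; the session and the Fitbit are described after that. Section 3.2.3.2 fixes the next contact: "Timepoint two is the second study contact and will take place at around 6-8 weeks postnatal when women attend routinely for OGTT". The Slimming World voucher is offered to the intervention arm at that contact. Text messages and monthly calls are described there or later.

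Section 3.3.1 states that "Primary and secondary outcomes at 12 months will be compared between the intervention and control groups", by analysis of covariance adjusted for baseline and centre, with a standard-error correction for randomisation by week. Section 3.1.4 says that blinding is not possible, and section 3.2.5 says that researchers administer all instruments.

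**The concern.** The stated purpose is causal, but the measurement attached to it has no control. Women who know their allocation answer the same two questions on either side of a one-hour session led by staff trained in motivational interviewing. Any change mixes the effect of the session with the effect of being asked twice, the wish to give the educator a welcome answer, and any drift between the two askings.

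The session is the main component delivered during pregnancy, and section 3.3.2 says that feedback on it will inform future trial design or roll-out. A rise read as a session effect could enter those decisions without support.

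Separately, the section says that the team wrote the motivation questions and then describes every questionnaire as having established reliability and validity. Both statements cannot stand as worded.

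**Working it through.** **1. The plan's own figure.** The article gives no scale, SD, target difference or test for motivation, so there is no figure to reproduce. Group sizes come from sections 3.1.2 and 3.1.7: 340 women allocated equally, so 340/2 = 170 per arm, and 100 per arm evaluable at 12 months.

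**2. What the one-arm change estimates.**

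mean change = session effect + repeat-asking effect + demand effect + drift

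One arm gives one equation, so the first term cannot be separated from the others.

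**3. How easily the other terms produce a significant result (illustration).** Set the session effect to zero and let the other terms sum to *s* SD units. With correlation *r* between the two answers, the SD of change is √(2(1−r)), and a paired test has

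z = s√n / √(2(1−r)), P(significant) = Φ(z − 1.96) + Φ(−z − 1.96).

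Example: s = 0.2, n = 100, r = 0.5 gives z = 0.2 × 10 / 1 = 2.0 and P = 0.516. The values of *s* and *r* are assumptions, and *r* runs from 0.3 to 0.7:

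| Non-session rise | n = 100 | n = 170 |
|---|---|---|
| 0.1 SD | 14% to 25% | 20% to 39% |
| 0.2 SD | 39% to 73% | 60% to 92% |
| 0.3 SD | 72% to 97% | 91% to over 99% |

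The nominal rate is 5%. The session comes soon after recruitment, so the number measured should be nearer 170 than 100.

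**4. Whether a randomised contrast can be formed from the planned data.**

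| | Intervention arm | Control arm |
|---|---|---|
| Timepoint one | motivation asked, described ahead of the session | motivation asked |
| Between | session and Fitbit | usual care |
| Timepoint two | motivation asked; voucher offered at the same contact | motivation asked |
| Later | voucher use, texts, calls | usual care |

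It can. Timepoint two is the one scheduled point at which the antenatal package can be compared as randomised before the postpartum components begin, provided the questions are answered before the voucher is offered.

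**5. Precision of that contrast.** Detectable difference at 80% power, two-sided 5%, ignoring week clustering: (1.96 + 0.842) × √(2/n) × √(1 − r²), where *r* is now the assumed correlation between timepoints one and two.

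- n = 100 per arm: 0.396 SD unadjusted; 0.378 SD (r = 0.3) to 0.283 SD (r = 0.7).
- n = 170 per arm: 0.304 SD unadjusted; 0.290 SD (r = 0.3) to 0.217 SD (r = 0.7).

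The larger number assumes no loss by timepoint two and is an upper limit. Section 3.1.1 reports high attrition at the corresponding visit in the pilot.

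**6. What that contrast means.** The session is at 32-36 weeks' gestation and timepoint two at 6-8 weeks postnatal. Assuming delivery at 40 weeks, the gap runs from (40 − 36) + 6 = 10 weeks to (40 − 32) + 8 = 16 weeks and spans the birth. The contrast covers session plus Fitbit, among women still in the study. Both arms are asked equally often and live through the same interval, so repeat asking and drift cancel. Demand effects from known allocation do not cancel.

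**The case against.** The strongest reply has four parts.

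- **Silence on timepoint two.** A reader might infer that the arms will be compared at 12 months only and that the timepoint-two scores will go unused. The article does not say so. Section 3.3.1 names the 12-month comparison without excluding others, and a condensed article may leave interim timepoints to an analysis plan that is not shown. This part stands, and the silence is not counted as an error.
- **No claim is planned.** A reader might also infer that a rise will be reported as a proven session effect. The article states a purpose but no test or conclusion, and the measure could serve as process evaluation beside the focus groups. This stands in part. The purpose as worded is still about influence, which a one-arm change cannot show, and a later analysis plan would not alter that.
- **The timepoint-two contrast answers another question.** It concerns a package, 10 weeks or more later, in retained women, and it leaves demand effects in place. This stands. The contrast supports the before-after measure and cannot replace an estimate of the immediate effect.
- **Drift may be negligible.** The timing of the second asking is not stated. If it follows directly after the session, drift is a weak threat. Repeat asking and demand effects remain.

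**Conclusion.** The point holds in a limited form. In an open trial with researcher-administered questions, a before-after change in the intervention arm alone cannot be attributed to the session, so the purpose stated in section 3.2.4.2 is not met by the measurement attached to it. The sentence on established validity also contradicts the account of the two motivation questions in the same section.

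The documents give nothing from which to size the bias. The percentages in the working show only that modest non-session shifts would often look like an effect; they depend wholly on assumed shifts and correlations. The detectable differences further assume no clustering by week.

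This is minor. It concerns a subsidiary measure within the secondary outcomes and leaves the primary outcome, the primary analysis and the sample size untouched.

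**What to change.** 1. In section 3.2.4.2, describe the before-after change as descriptive of the intervention arm, and replace the wording that gives it a causal purpose. State when the second asking takes place.
2. Add a supportive between-arm comparison of motivation at timepoint two: analysis of covariance adjusted for the timepoint-one score (taken before the session) and centre, with the correction for randomisation by week already planned in section 3.3.1. Have the timepoint-two questions answered before the voucher is offered.
3. State beside it that the comparison estimates the antenatal package (session plus Fitbit) at 6-8 weeks postpartum among women still in the study. Say that it is not the session's immediate effect, and that it removes repeat asking and drift but not demand effects from known allocation.
4. Exclude the two team-written motivation questions from the sentence on established reliability and validity.

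The cost is one added analysis of scores already scheduled in both arms, a fixed order of events at one contact, and small wording changes. No new visits, instruments or participants are needed. If an analysis plan already contains the timepoint-two comparison, only the wording and the order of events remain to be settled.
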